### Quality control

Calibration procedure and frequency for the weighing machine, BP apparatus, POC kits for capillary RBG and HbA1c and urine will be followed at all centres to avoid any bias or errors. All personnel involved in the grading of retinal images must have completed a study-specific training course.

### Data management

The data will be entered directly by the fieldworkers into a tablet that is linked to a cloud-based electronic database hosted in India. In situations where internet access is not available, paper case report forms will be used at the site and later transcribed into the database. The data in the database will be monitored by the study monitoring team. The retinal photographs will also be uploaded to the platform. The WHO STEPwise approach to surveillance will be used to develop the cloud-based electronic database.^27^ The study is monitored by an independent committee and the progress of the study is reviewed by the grant executive committee.

### Database functionality and quality assurance

The study electronic database (Playon, Bangalore, India) will be hosted on a dedicated secure server in India. All data will be managed through this system. The database will be programmed to perform validation checks, such as range checks to prevent data entry errors, missing data to be flagged up to ensure completion of the data entry. The system will provide for data security and also have formal database lock functionality and it will support real time data cleaning and reporting.

### Statistical considerations

The statistical methods will be developed fully within a statistical analysis plan, to be finalised before database lock. Diagnostic accuracy publications will follow recognised Standards for Reporting Diagnostic accuracy studies guidelines and the observational component will follow the Strengthening the Reporting of Observational Studies in Epidemiology guidelines. Table 1 shows the reference and index tests for diagnostic accuracy aspect of the study.

**Table 1 T1:** Reference and Index tests

Community screening for diabetes	
Reference standard	Index test
1. RBG	POC HbA1c Non-invasive diabetes risk scores
Community screening for prediabetes	
1. POC HbA1c	RBG Non-invasive diabetes risk scores
Community screening for complications of diabetes	
1. Serum lipid profile TC Non-HDL cholesterol LDL cholesterol HDL cholesterol TC:HDL ratio Triglyceride	Risk-based screening tool for complications of diabetes using minimally or non-invasive tests
2. HbA1c or RBG	
3. Microalbuminuria	
4. Retinal photography for retinopathy for all people with diabetes	

HbA1c, glycated haemoglobin; HDL, high density lipoprotein; LDL, low density lipoprotein; POC, point-of-care; RBG, random blood glucose; TC, total cholesterol.

Accuracy will be measured by sensitivity and specificity of tests to detect diabetes, prediabetes and people at risk of complications of diabetes. Clustering will be used to accommodate any over dispersion. Consistency of these statistics will be explored across centres and clusters (urban, rural and special population). Area under receiver operating characteristic (ROC) curve will be used to compare models representing the overall performance of tests under comparison. Refinement of test components (eg, combinations of tests or questionnaire items) will be developed, and internally validated where sufficient data are available. The number of false positives will be identified directly from the data. From the estimates of sensitivity and the specificity of diabetes risk score to detect prediabetic (or diabetic) and its estimated prevalence, it will be possible to estimate the false positive rate and the complement of the positive predictive value. All estimates will be accompanied by estimated 95% CIs, which account for both clustering and stratification.

For the modelling framework, a marginal model with a logit link will be used, with retinal photograph determination of the reference outcome. Model-predicted probabilities will enable the area under the ROC curve to be estimated with 95% CI allowing for clustering, and accompanied by estimates of sensitivity, specificity, predictive values and likelihood ratios. Diabetes alone, and diabetes or prediabetes will be explored, as will already-identified and newly identified diabetes. For research questions on the diabetes diagnostic model, the denominator will principally be all those diagnosed with diabetes, whether already diagnosed or newly diagnosed. Interaction with this term (known vs newly diagnosed) will contribute to the analysis involving costs. Further modelling will explore use of the data from those that were found not to have diabetes or prediabetes.

Marginal logistic modelling will be used to identify the tests and questionnaire items which are most predictive, following a recommended approach.^28^ Continuous predictors will be handled using the fractional polynomial approach.^29^ In the sample size section, it can be seen that the dataset is large enough to allow models to assess up to 10 (reliably) and 20 (less reliably) dependent on intracluster correlation. Differences in area under the ROC curve and differences in specificity for given sensitivity will be estimated. The sample size is large enough to assess existing tests and to develop models. There may be limited scope to validate models. However, interim analysis will allow assumed rates and numbers to be assessed; the number of cases with STDR will be estimated more accurately, and this may enable more sophisticated forms of internal validation. Model validation would include calibration after model discrimination.^30^ Clustering within estimates of sensitivity, specificity and areas under the ROC curves will account for clustering, considering use of the non-parametric stratified bootstrap. A similar approach will be undertaken for the model to identify people at risk of complications of diabetes. Models for DR will also test the accuracy of artificial intelligence graded images compared with human graders.

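### Internal validation of the developed models depends on having enough data, so optimism correction may be dropped when events are few and it is most needed

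*Protocol article*

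**What the plan says.** The Statistical considerations section of the protocol article plans to refine tests, for example by combining tests or questionnaire items, and says the results will be "internally validated where sufficient data are available". The modelling paragraphs of that section add: "There may be limited scope to validate models". An interim analysis is to give a better estimate of the STDR count, and "this may enable more sophisticated forms of internal validation". The strengths and limitations box also concedes that some models may go unvalidated.

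The same section says that marginal logistic models will pick out the most predictive tests and items, with fractional polynomials for continuous predictors, and that up to 10 covariates can be assessed reliably and 20 less reliably.

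On precision, the section makes a general commitment: "All estimates will be accompanied by estimated 95% CIs, which account for both clustering and stratification". It repeats this for the "area under the ROC curve to be estimated with 95% CI allowing for clustering". For sensitivity, specificity and AUC it mentions one technique, tentatively: "Clustering within estimates of sensitivity, specificity and areas under the ROC curves will account for clustering, considering use of the non-parametric stratified bootstrap". It does not say what the strata are or what unit is resampled. Full methods are left to a statistical analysis plan to be finalised before database lock.

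**The concern.** A model whose items and functional forms are chosen on a data set looks better on that data set than on new people. The gap, the optimism, widens as the number of events per candidate predictor falls. A rule that validates only when data are plentiful therefore allows correction to be left out where the bias is largest, and keeps it where it matters least. This is a stated decision rule, not a detail merely left to the analysis plan.

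The condition would make sense for a split sample or a held-out set of regions, which use up cases. It does not make sense for a bootstrap optimism correction, which uses the development data themselves and can be run at any event count.

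The stakes go beyond one reported AUC. The Health economics analysis plan section compares screening pathways that include whichever new method the statistical modelling finds accurate, and it takes true and false positive and negative rates from the study data. Optimistic accuracy would favour the new pathway over its comparators. The Objectives section also foresees region-specific risk models if numbers permit, and those would have far fewer events than the national model.

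**Working it through.** **Step 1. Reproduce the plan's event count** (Sample size calculation section).
- DR cases: 4800 × 0.30 + 4800 × 0.15 = 1440 + 720 = 2160.
- STDR cases: 216, which is 216 / 2160 = 10% of DR cases.
- Design effect: 1 + (100 − 1) × 0.075 = 8.425. The stated 8.5 equals 1 + 100 × 0.075.
- Effective STDR cases: 216 / 8.5 = 25.4, stated as 25.

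The chain reproduces. The 25 is stated for covariates that are constant within a region or highly correlated among families in an area. It is not the planned number of events for participant-level covariates. It serves below as a low-information case.

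**Step 2. Events per candidate.**
- 216 events: 216 / 10 = 21.6 and 216 / 20 = 10.8.
- 25 events: 25 / 10 = 2.5 and 25 / 20 = 1.25.
- For scale, a single region would expect 216 / 20 = 10.8 STDR cases in total.

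**Step 3. Size of the optimism.** Optimism = apparent AUC − AUC in new data. The documents give no predictor strengths, so these are assumed: independent standard normal predictors, three of them with a log odds ratio of 0.5 per standard deviation and the rest null. All candidates enter a logistic model as linear terms. Each fitted model is evaluated in 40,000 new people, with 40 simulated data sets per row.

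| People with diabetes | Mean events | Candidates | Apparent AUC | New-data AUC | Optimism |
|---|---|---|---|---|---|
| 9600 | 209 | 10 | 0.733 | 0.719 | 0.013 |
| 9600 | 208 | 20 | 0.742 | 0.716 | 0.026 |
| 1111 | 25 | 10 | 0.760 | 0.685 | 0.075 |
| 1111 | 24 | 20 | 0.816 | 0.653 | 0.163 |

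(The first row's optimism was computed before rounding.)

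With the same candidates, optimism is about six times as large at about 25 events as at about 210: 0.075 / 0.013 = 5.8 and 0.163 / 0.026 = 6.3. If the model at low event counts were cut to two candidates, both truly predictive (log odds ratio 0.6), optimism was only 0.008 at about 23 events. The large figures therefore belong to searching 10 to 20 candidates on few events, not to few events alone. The simulation includes neither item selection nor fractional polynomials, so it does not measure what those steps would add.

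**Step 4. Does the resampling unit matter?** For the AUC, three bootstrap schemes were simulated with 20 regions of 480 people, about 200 events and an outcome ICC of 0.075. The bootstrap standard error was about 0.018 when individuals were resampled within strata and 0.017 to 0.019 when regions were resampled, against a true standard deviation of 0.019. The difference is small.

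Specificity could be more exposed. With 9600 − 216 = 9384 people without STDR, or 9384 / 20 = 469.2 per region, and an assumed specificity of 80%, the half-width ignoring clustering is 1.96 × √(0.8 × 0.2 / 9384) = 0.81 points. Multiplying by the square root of 1 + (469.2 − 1) × ICC gives 1.9, 2.6, 4.0 and 4.9 points at ICCs of 0.01, 0.02, 0.05 and 0.075. The ICC of test positivity is not in the documents, so this range is an assumption. It shows only what would follow if clustering were ignored.

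**The case against.** The best defence of the plan has three parts.

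First, the condition is attached to refinement of test components, and the interim wording speaks of more sophisticated validation, which leaves room for simpler forms whatever the count. The plan also foresees calibration as part of validation, explores consistency across centres, and openly discloses the limitation. Nothing says that the apparent AUC will be the reported figure. This stands in part: upward bias is a risk that the rule permits, not a certainty. But combinations of tests and items are the developed models, and no optimism correction is promised unconditionally anywhere.

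Second, at the planned event count and number of covariates the bias is modest. This stands. Larger values need inputs that the plan does not contain, such as 40 screened items or univariable selection.

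Third, a reader might infer from the bootstrap sentence that individuals will be resampled within strata, so that region-level correlation is lost and intervals come out too narrow. The article does not support this. The method is only under consideration and no unit is named. A stratified bootstrap can draw clusters within strata, and the same section commits all intervals to reflect clustering. Naming the unit is ordinary analysis-plan detail. The sentence is circular, and the Sample size calculation section treats two urban, rural and special-population terms as a further way to accommodate clustering. It is therefore worth naming the unit, but its absence is not an error.

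**Conclusion.** The concern holds for validation. Making internal validation conditional on enough data allows correction to be omitted where overfitting is worst, although the correction needs no new data. Under assumed predictor strengths, an uncorrected AUC would be about 0.01 to 0.03 too high with 10 to 20 candidates and about 210 STDR events, and about 0.08 to 0.16 too high with the same candidates at about 25 events. Other predictor strengths, and the effect of selection and fractional polynomials, would change these values; more optimism with fewer events per candidate would remain. The point bears mainly on the STDR model and any smaller models. Outcomes with many more events are less affected.

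It does not extend to the confidence intervals. They would be too narrow only if individuals were resampled or clustering otherwise ignored, which the article does not say. This is a change worth making before the analysis plan is final, not a flaw that invalidates the study.

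**What to change.** 1. Delete the condition on sufficient data. State that every developed model will be internally validated by bootstrap whatever the STDR count.
2. In each resample, repeat the whole model building, including item selection and fractional polynomials. Report the optimism-corrected AUC and the calibration slope beside the apparent values.
3. Draw those resamples at cluster level (primary sampling units or regions, within strata) and name the unit in the analysis plan. The intervals then meet the commitment on clustering and stratification already made. Replace the circular bootstrap sentence accordingly.
4. Feed the corrected accuracy into the economic model.

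The cost is programming and computing time, and slightly lower reported AUCs. No new data are needed.

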### Sample size calculation

The sample size is determined by considering the numbers of expected STDR, as this analysis will have the smallest number of cases with the outcome. With 20 regions, we expect 216 cases of STDR. From 48 000 people (2400 per centre) screened, of whom about 4800 are expected to be known diabetes and, we suspect, another 4800 will be newly detected diabetes. As 30% of the former group, and 15% of the latter group, are expected to have DR, we anticipated 2160 people to have DR, of whom 216 to have STDR.

Considering that some patients would come from the same family, and some from the same area, we assumed that outcomes at the area level would have an allowed intracentre correlation (ICC) coefficients of approximately up to 0.05 and to 0.10 for new and known diabetes, respectively. At the area level, with approximately 100 cases per region, and a working ICC of 0.075, we expect a design effect of 8.5. This calculation has been based on conservative allowances and approximations, which allow for deviations in the actual intracluster correlation coefficients from those anticipated, or for variation in the actual number of cases across centres. This means that the effective sample size (were the sample to be free from clustering) is 25 STDR cases for covariates, which are constant at the region level, or highly correlated among families within the same area. Using the rule of 10 people per covariate in order to plan the number of possible covariates, this implies that it will be possible to include 10–20 covariates (216/10) at the participant-level dependent on whether there is no, modest or moderately high ICC in the covariates, and 1–2 covariates (25/2) either at the area/family level for a stable diagnostic STDR model. All models will include observations at the participant level in order to accommodate participant-level covariates and will accommodate clustering further by including two area contrast terms; these reflect whether a participant lives in the strata of regions that are urban, rural or a special population. Models will be from the ‘marginal’ class so that correlation can be accommodated while importantly retaining a participant-specific interpretation of resulting estimates. The study will continue to recruit to enable process evaluation and other substudies to be incorporated.

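### The design effect of 8.5 is built on about 100 unlabelled cases per region, not the roughly 480 people with diabetes analysed there, so 25 effective STDR cases and 1–2 region-level covariates are not supported at the plan's own ICC

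*Protocol article*

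**What the plan says.** All of the sizing is in the Sample size calculation section of the protocol article.

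- Events: "With 20 regions, we expect 216 cases of STDR". The section starts from 48 000 people screened, "of whom about 4800 are expected to be known diabetes and, we suspect, another 4800 will be newly detected diabetes". Then: "As 30% of the former group, and 15% of the latter group, are expected to have DR", and "we anticipated 2160 people to have DR, of whom 216 to have STDR".
- Clustering: ICCs of up to about 0.05 for new and 0.10 for known diabetes are allowed for, and "with approximately 100 cases per region, and a working ICC of 0.075, we expect a design effect of 8.5". The section describes its allowances as conservative.
- Result: 25 effective STDR cases for covariates that are constant at region level or highly correlated among families in an area.
- Covariate budget, with a rule of 10 people per covariate: 10–20 at participant level, printed as 216/10, and "1–2 covariates (25/2) either at the area/family level for a stable diagnostic STDR model".

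On who is analysed, Table 1 gives retinal photography to all people with diabetes. The paragraph of Statistical considerations that sets a retinal reference outcome says that "the denominator will principally be all those diagnosed with diabetes", known or new. That sentence opens by referring to the diabetes diagnostic model, so it supports the STDR denominator less directly than Table 1 does.

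**The concern.** A design effect for a covariate that takes one value per region depends on how many analysed people share that value. The STDR model is fitted to people with and without STDR, so the non-cases count towards cluster size. The plan's figure of about 100 per region is neither the people analysed (480) nor the STDR events (10.8). The only nearby count in the section is any diabetic retinopathy (DR), at 108, but the text never says that this is what was meant.

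The 25 effective cases, and the statement that 1–2 area-level covariates give a stable model, both rest on this choice. If the cluster size is too small, the plan permits region-level predictors that its own rule of 10 would not allow, and the description of the calculation as conservative is wrong for those predictors.

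**Working it through.** **Inputs** (Sample size calculation, unless noted)

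- 20 regions; 4800 + 4800 = 9600 people with diabetes.
- DR: 0.30 × 4800 + 0.15 × 4800 = 1440 + 720 = 2160. STDR: 216.
- Working ICC 0.075; stated range 0.05 to 0.10.
- Rule: 10 per covariate.
- Retinal photography for all people with diabetes (Table 1).

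**Formulae.** Design effect DE = 1 + (m − 1) × ICC, with m the cluster size. Effective STDR cases = 216/DE. Region-level covariates supported = effective cases/10.

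**Step 1: the plan's figure.** With m = 100, DE = 1 + 99 × 0.075 = 8.43; m = 101 gives exactly 8.5. Then 216/8.5 = 25.4. The printed 8.5 and 25 therefore follow from the printed inputs.

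**Step 2: what m could be.** Per region, the plan's totals give 9600/20 = 480 people with diabetes, 2160/20 = 108 with DR and 216/20 = 10.8 with STDR.

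**Step 3: what m should be.** If m people in a region each have outcome probability p, the variance of the region's event count is m·p(1 − p)[1 + (m − 1)ICC]. Here m counts everyone contributing an observation, not the events alone. For an STDR model fitted to people with diabetes, m = 480.

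**Step 4: results at ICC 0.075**

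| Cluster size m | DE | Effective STDR cases | Covariates at 10 each |
|---|---|---|---|
| 10.8 (STDR cases) | 1.7 | 124.5 | 12.5 |
| 100 (as printed) | 8.4 | 25.6 | 2.6 |
| 108 (DR cases) | 9.0 | 23.9 | 2.4 |
| 480 (people with diabetes) | 36.9 | 5.8 | 0.6 |

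As a cross-check on the last row, 9600/36.925 = 260 effective people, and 260 × 216/9600 = 5.85 effective cases.

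**Step 5: the stated ICC range, m = 480.** ICC 0.05 gives DE 24.95 and 8.7 effective cases (0.9 of a covariate). ICC 0.10 gives DE 48.9 and 4.4 cases (0.4). Neither end reaches one covariate.

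**Step 6: the ICC that would rescue 8.5.** (8.5 − 1)/(480 − 1) = 7.5/479 = 0.016, below the stated range.

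**Step 7: the printed division.** 25/2 = 12.5, which is not 1–2. The stated rule gives 25/10 = 2.5.

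**The case against.** The strongest objection is to the ICC. The stated values are upper allowances given for new and known diabetes, and none is specific to STDR. STDR is expected in 216/9600 = 2.25% of people with diabetes. On the proportion scale, an ICC of 0.075 implies a between-region SD of √(0.075 × 0.0225 × 0.9775) = 4.1 percentage points, about 1.8 times the mean, which is large. At an ICC of 0.016 the SD is about 1.9 points, and a design effect of 8.5 would hold with m = 480. So 8.5 may turn out to be adequate. That stands as a reason not to treat 6 effective cases as established. It does not rescue the text, which adopts 0.075 and offers no smaller value.

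Other structures are also less severe. Treating known and new diabetes separately (240 each per region, ICC 0.10 and 0.05, and assuming STDR splits 144/72) gives 5.8 + 5.6 = 11.3 effective cases. Adding them assumes that the two groups in one region are uncorrelated. Clustering at the 60 sampling clusters (160 people with diabetes each) gives DE 12.9 and 16.7 cases at ICC 0.075, or 24.1 at ICC 0.05. That calculation suits covariates varying between clusters, whereas the 25 is stated for covariates constant across a region. The plan describes neither structure.

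Stronger readings are tempting, and the document does not support them:

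- **The whole covariate budget is wrong.** The upper participant-level figure, 216/10, does not use the design effect and stands. The lower end of 10 may depend on cluster size, but its derivation is not shown and no covariate ICC is given, so no replacement range can be computed from the document.
- **The mandatory contrasts exhaust the region-level budget.** The plan says that models "will accommodate clustering further by including two area contrast terms", for urban, rural and special populations. Study setting places one cluster of each kind in every region, so these contrasts vary within region and are not the region-constant covariates that the 25 describes.
- **The plan used the DR count.** This is an inference from 108 being close to 100.

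It is also fair that no region-constant predictor is named, and that the Statistical considerations section warns of limited scope for validation and provides for interim reassessment of rates.

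**Conclusion.** The point holds for region-constant covariates. The arithmetic is right on its inputs, but the cluster size is not the one the STDR analysis implies. At the plan's own ICC of 0.075 the effective number of STDR cases is about 6, so 25 is overstated roughly fourfold. Across the plan's range it is about 9 to 4, and no region-level covariate is supported under its rule of 10. The 1–2 region-level covariates and the conservative label therefore do not hold as written. The 25/2 is a separate misprint with no further effect.

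This rests on the STDR model being fitted to all people with diabetes (Table 1, and less directly Statistical considerations), on roughly equal regions, and on the stated ICCs applying to STDR. A justified STDR-specific ICC near 0.016 would restore a design effect of about 8.5. Nothing here shows that the study is too small for its stated aims, or that the participant-level budget is wrong at its upper end.

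**What to change.** Revise the clustering paragraph of the Sample size calculation section:

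1. State what the cases per region are.
2. Recompute the design effect with the number of people analysed per region (about 480), using either the stated ICC or an STDR-specific ICC with its justification.
3. Restate the effective STDR cases and the region-level covariate budget. At ICC 0.075 that is about 6 cases and no region-level covariate. Keep the conservative label only if the new figures support it.
4. Replace 25/2 with 25/10 or its recomputed equivalent.
5. Show how the lower end of the 10–20 participant-level range is obtained, and revise it if it uses the same cluster size. Leave 216/10 as the upper end.

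The cost is one rewritten paragraph and a less favourable stated figure. No extra recruitment is called for. The change should be made before candidate predictors for the STDR model are chosen.

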## Abstract

**Introduction:**

The aim of this study is to develop practical and affordable models to (a) diagnose people with diabetes and prediabetes and (b) identify those at risk of diabetes complications so that these models can be applied to the population in low-income and middle-income countries (LMIC) where laboratory tests are unaffordable.

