### Study setting

This community screening will be conducted across 20 regions in India, each led by a local clinical centre with a trained ophthalmologist responsible for the study at that site (figure 1). Each region will have three clusters stratified into urban, rural and a predefined special category of population such as people with poor access to healthcare, or persons that are presumed to be at high risk or low risk of developing diabetes. The study will involve a door-to-door survey, with questionnaires and POC tests performed by fieldworkers. Each cluster will screen at least 800 consenting individuals aged 40 years or above for a cumulative sample size of a minimum of 48 000 participants. If any cluster or centre does not reach their target recruitment, it will be made up by another cluster or centre with the same stratified population.

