### Stratified sampling

In each region, we predefined a geographic area as urban or rural based on a multistage sampling technique using data from the 2011 census of India. A census enumeration block that usually consists of 125–150 households with a population of 650–700 is the primary sampling unit for urban areas, while villages are defined in the rural areas. Bigger villages are further divided to ensure that approximately 300 households can be covered. The house-to-house survey will be conducted by approaching each household in consecutive streets in each area. If the household members are not available, a further two visits by the fieldworkers are permitted. In each household, all available members aged 40 years or above, who meet the inclusion criteria, will be invited to participate in the study.

The special category groups include two groups: (a) people working under high stress leading to poor and untimely eating habits (such as policemen, truck and taxi drivers, manual labourers, fishermen, factory staff and professionals in stressful jobs) and those presumed to be at low risks such as certain religious groups and (b) people with poor health seeking behaviour and/or under social stigma (such as tribal, slum population and people with infection like HIV or leprosy). All survey clusters and special groups are independent samples. The total population for the study is the total recruited participants in all the 20 regions, including the special population (figure 1).

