### Selection of participants

The inclusion criteria are adults who are ≥40 years of age (special groups may contain adult population of any age), who are local residents of Indian origin and are willing to give informed consent (see online supplemental appendix 1 for sample informed consent form).

10.1136/bmjopen-2020-039657.supp1Supplementary data

Exclusion criteria include vulnerable adults in whom it may not be possible to carry out all the tests; pregnant and breastfeeding women; anyone in the opinion of the fieldworkers deemed too ill to be screened; and those who are currently participating in intervention trials with investigational medicinal products.

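### All models carry an urban/rural/special contrast, but 'special' is a study-defined mix that a user elsewhere cannot assign consistently, so the main performance figures should come from the model without it

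*Protocol article*

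**What the plan says.** All references are to the protocol article.

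- **Sample size calculation.** All models "will accommodate clustering further by including two area contrast terms", and "these reflect whether a participant lives in the strata of regions that are urban, rural or a special population". The terms are mandatory and come on top of marginal models chosen to handle correlation.
- **Statistical considerations.** The AUC, with sensitivity, specificity, predictive values and likelihood ratios, is obtained from model-predicted probabilities. Calibration is part of model validation. Confidence intervals are to allow for clustering and stratification. "Consistency of these statistics will be explored across centres and clusters (urban, rural and special population").
- **Study setting.** The special stratum is chosen from "people with poor access to healthcare, or persons that are presumed to be at high risk or low risk of developing diabetes".
- **Stratified sampling.** Group (a) puts people in high-stress work together with "those presumed to be at low risks such as certain religious groups". Group (b) covers people with poor health-seeking behaviour or social stigma, such as tribal and slum populations.
- **Selection of participants.** The age limit of 40 is relaxed here: "special groups may contain adult population of any age".
- **Abstract, Introduction.** The models are developed "so that these models can be applied to the population in low-income and middle-income countries".

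Nothing in the article removes the contrasts, fixes them or averages over them when predictions are made, or says how a user outside the study would set them.

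**The concern.** A prediction tool needs inputs that its user can supply. Someone applying the model in another country can usually say whether a person lives in an urban or a rural area. They have no rule for 'special', because membership was decided by which group a study centre chose to sample. A slum resident or a taxi driver could reasonably be entered as urban or as special. The predicted risk then depends on an arbitrary choice, and calibration cannot be stated for that person.

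A second consequence is possible but less certain. If the special stratum differs in risk after the other predictors, the contrast adds discrimination that the deployed tool will lack, so the study AUC is too high for that use. This matters because models are compared by AUC, and the health economics plan carries forward the approach found accurate.

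Third, a consistency check on a stratum that mixes presumed high and presumed low risk can average opposite effects and look reassuring.

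**Working it through.** **1. The plan's own figures.** DR cases: 0.30 × 4800 + 0.15 × 4800 = 2160. STDR cases: 216, which is 10% of 2160 (implied, not stated). Denominator: 4800 + 4800 = 9600 people with diabetes. STDR risk: 216/9600 = 2.25%. Strata: 20 regions × 3 clusters × 800 = 48 000, so urban, rural and special are planned in equal size. The article states no AUC, so there is none to reproduce.

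**2. Effect on an individual's predicted risk.** Take a person with risk 2.25% when coded as non-special: odds = 0.0225/0.9775 = 0.02302.
- Odds ratio 1.35 for special: 0.02302 × 1.35 = 0.03107, risk 0.03107/1.03107 = 3.0%.
- Odds ratio 2.0 for special: 0.02302 × 2 = 0.04604, risk 0.04604/1.04604 = 4.4%.

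The same person has a predicted risk of 2.25% or of 3.0% to 4.4%, depending on a label with no rule outside the study.

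**3. Effect on AUC.** My assumptions: one participant-level score s, normal with log-odds SD 0.75; three equal strata; overall risk 2.25%; only special differs, with log odds ratio b. The model is logit(p) = a + s + b × special, with a solved so that the mean risk is 2.25%. I compared the AUC when people are ranked by s + b × special with the AUC when they are ranked by s alone.

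| Odds ratio for special | AUC with term | AUC without | Excess |
|---|---|---|---|
| 1.35 | 0.704 | 0.701 | 0.003 |
| 1.65 | 0.710 | 0.700 | 0.010 |
| 2.0 | 0.718 | 0.700 | 0.018 |

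The last excess is 0.018 by numerical integration; a second run of the same set-up gave 0.019. The result depends on how strong the other predictors are. At odds ratio 2 the excess is 0.026 if the within-stratum AUC is 0.65, 0.013 if it is 0.75, and 0.006 if it is 0.85. It is zero if special does not differ.

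**4. If opposite risks are mixed within special.** Let half of special have odds ratio 2.0 and half 0.5. The risks are 4.40% and 1.14%, with mean (4.40 + 1.14)/2 = 2.77%. The pooled odds ratio is (0.0277/0.9723)/0.02302 = 1.24. With the score of step 3 included, the pooled contrast raises the AUC by only about 0.002. So the mixing that makes the label hard to interpret also removes most of the AUC excess, while the single coefficient of 1.24 describes neither half.

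**5. Can special be split?** With equal shares, each of three types of special group has 216/(3 × 3) = 24 STDR cases, before any design effect. For any DR it is 2160/(3 × 3) = 240.

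**The case against.** **The article does not say that the contrasts are active when the final AUC is computed.** They appear only under sample size, and the text on model building speaks of tests and questionnaire items. The statistical analysis plan is not shown and could average over them. This stands as a limit: a reader might infer that the published AUC will certainly be inflated, and the document does not establish that. It does fix two things, terms in all models and performance from those models' predictions, and on a plain reading the two combine.

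**Clustering is already handled.** A reader might infer that the plan relies on three fixed area types to absorb correlation within regions. It does not. The contrasts are a further step beside marginal models, a possible stratified bootstrap, and intervals that allow for clustering and stratification. That reading falls.

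**The AUC effect is small.** With 216 cases among 9600, an AUC of 0.70 has a Hanley-McNeil 95% half-width of about 0.04 before clustering, and the excess lies inside it. A larger figure, 0.01 to 0.04, results if all contrasts are dropped and strata differ in opposite directions by odds ratios of 1.35 to 2.0. But urban/rural is available to users, so that figure does not measure the problem. This objection stands on size. It does not touch the undefined predicted risk.

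**The groups exist elsewhere.** Slum, tribal and driver populations are not unique to this study. True, but the combined label has no rule for assigning a given person to it.

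**Stratum consistency is already to be explored.** This is a partial safeguard, weakened because special is treated as one group.

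**A pooled AUC without the contrast still reflects the study's equal stratum mix.** Correct. It is nevertheless the accuracy of a model that can be applied.

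**Conclusion.** The point holds in a limited form. The firm part needs no simulation: a mandatory model term is defined by study sampling, pools groups with opposite presumed risk, and cannot be set consistently by the intended users. Predicted risk and calibration are therefore undefined for them.

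The AUC part is conditional and modest: about 0.003 to 0.019 for odds ratios of 1.35 to 2.0, given a log-odds SD of 0.75, STDR risk of 2.25%, equal strata and only special differing. It is about 0.002 if odds ratios of 2.0 and 0.5 offset each other within special. The odds ratios and the SD are my assumptions, since the article gives neither. A reader might infer that substantial AUC inflation and cancelling of opposite risks occur together. They pull against each other, and the documents do not show which will prevail.

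This is an inexpensive improvement to the reporting of the models and no ground for rejecting the modelling approach.

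**What to change.** State that the main reported AUC, sensitivity, specificity and calibration come from the model without the special contrast; the urban/rural contrast may stay. Show the model with all contrasts as a sensitivity analysis. Keep clustering and stratification in the variance as already planned.

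For the more common outcomes (diabetes, prediabetes, any DR), and where numbers allow, show the consistency analysis by recorded type of special group: high-stress occupation, presumed low risk, and poor access or stigma. Do not require this split for STDR, where about 24 cases per type would be uninformative.

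The cost is one extra model fit on data already collected, a finer consistency table for some outcomes, and a slightly lower reported AUC.
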